# A coadapted community-based participatory group programme for parents/carers of children with complex neurodisability (Encompass-2): a pilot and feasibility study protocol

**DOI:** 10.1186/s40814-025-01619-3

**Published:** 2025-05-03

**Keywords:** Neurodevelopment, Neurodisability, Cerebral palsy, Community-based programmes, Child(ren), Caregivers, Peer support, Co-design, Feasibility, Acceptability

## Abstract

**Background:**

Parents/carers of children with complex neurodisability continue to lack appropriate family-centred care. “Encompass” is a community-based group programme that was co-adapted from “Baby Ubuntu” in Uganda. It is an example of a “decolonised healthcare innovation” as it is a low-cost solution from a low-income country for use in a resource-constrained UK National Health Service (NHS).

**Methods and analysis:**

We will conduct a mixed-methods pilot feasibility study to determine the feasibility and acceptability of delivering and evaluating “Encompass” with parents/carers of children under 5 years with complex neurodisability in the UK. We aim to recruit 20 parents/carers of children from two NHS trusts in England serving urban areas where there is high social deprivation and ethnic diversity. Recruited parents/carers will attend the 10-modular, participatory group programme over a 6-month period. Groups will be facilitated by a trained allied health professional and an “expert parent” with lived experience. The primary outcomes of interest are the feasibility of delivering and evaluating the programme (recruitment, retention rates, acceptability as perceived by the parents/carers, facilitators and wider key NHS partners), intervention fidelity and participant adherence. Results will be collectively assessed against traffic light criteria. Pre-, post- and follow-up data collection questionnaires will include the Family Empowerment Scale (FES), the Power Ladder Question, the Parent Patient Activation Measure (P-PAM), Warwick-Edinburgh Mental Wellbeing Scale (WEMWBS), EuroQoL-5D-5-level (EQ-5D-5L) and parent/carer greatest needs and goals questionnaire. Post-intervention semi-structured interviews will be conducted with parents/carers, facilitators and key NHS partners.

**Discussion:**

A community-based participatory group programme is a potentially affordable and sustainable way for the NHS to provide family-centred support. The programme aims to improve outcomes for parents/carers of children with complex neurodisability. Example outcomes include knowledge, skills, confidence, wellbeing and quality of life. The programme also provides opportunities for peer support and aims to empower parents/carers in navigating community health systems.

**Registration:**

The protocol is registered on clinical trials.gov (ID: NCT06310681).

**Ethical approval:**

Health Research Authority ref. 23/EM/0213.

**Supplementary Information:**

The online version contains supplementary material available at 10.1186/s40814-025-01619-3.

## Background

The term neurodisability is commonly used in the United Kingdom (UK) to refer to a group of children or young people with long-term health conditions due to a neurological cause that results in functional impairments in their daily life [1]. An example of a complex neurodisability is cerebral palsy (CP), which describes a group of disorders that are caused by damage to the developing brain not only affecting movement and posture but also providing a range of possible developmental challenges in the form of musculoskeletal, cognitive, sensory, behaviour and communication difficulties [2].

Parents/carers raising children with complex neurodisability face numerous challenges, particularly during key transition periods including the time just after diagnosis. There is a deluge of evidence that explores the physical, psychological and practical challenges that they face [3–7] along with well-established evidence that holistic, family-centred care is best practice [8]. There remains an implementation gap as families continue to describe challenges in accessing appropriate family-centred care. This was demonstrated in a preliminary study (Encompass 1) undertaken in one of the sites where this pilot and feasibility study will take place [9]. In Encompass 1, parents/carers described the challenges in communicating with healthcare professionals, finding the appropriate medical jargon-free information that they require about their child’s diagnosis and services available, and the lack of joined-up holistic care in the community [9].

The study will take place in two urban boroughs in England where there is high social deprivation and ethnic diversity. Those residing in these areas experience significantly higher prevalence of poor mental and physical health, as well as higher service use compared to the UK [10, 11]. One of the boroughs has the lowest proportion of first-language English speakers compared to all local authorities across England and Wales [12]. Both boroughs have higher rates of children living in poverty (44% and 48% of children) compared to the average rate of 33% of children in the city [13]. Health literacy is another example of a health inequality that parents/carers experience in these areas, which can result in poorer health outcomes for their child [14]. The prevalence for low health literacy nationally is 41%, while the prevalence for the study sites is 67% and 58% [15].

To address aspects of this implementation gap in providing appropriate family-centred care, there are a number of parent/carer group programmes being developed and tested in high-income countries globally which include “Healthy Parent Carers” [16, 17], “ENVISAGE (ENabling VISions and Growing Expectations)” [18, 19], “Healthy Mothers, Healthy Families” [20] and “Parenting Acceptance and Commitment Therapy (PACT)” [21]. These programmes target families who have children with a variety of developmental disabilities, and each has slightly differing aims and objectives. Another example of a parent/carer group programme for families of children with complex neurodisability is the “Ubuntu” model. Unlike the other programmes described, “Ubuntu” was initially developed for children with cerebral palsy and those with complex motor disorders, rather than being agnostic about diagnosis. The “Ubuntu” programme includes the children themselves within the group which is another key difference compared to the other programmes. It is therefore more targeted to meet the specific needs of families who have children with complex neurodisability, which is why it was chosen for this study.

Ubuntu (previously known as “Getting to know Cerebral Palsy”) is a community-based participatory caregiver group programme that has been tested in resource-limited settings such as Uganda, Ghana and Bangladesh and has been implemented in low- and middle-income countries globally. Evaluations of this programme demonstrated improvements in parental confidence and self-efficacy, as well as improved quality of life (QoL) for children with cerebral palsy and their families [22–24]. The modular, facilitated, participatory programme is comprehensive in that it aims to promote inclusion and participation for the child with a neurodevelopmental disability (such as CP) in the community, to maximise the child’s health and development, to empower caregivers through information sharing and peer support, to address stigma and to promote the human rights of children with disabilities. The Encompass 1 study also explored the theoretical acceptability and feasibility of adapting and implementing the “Ubuntu” programme in the UK. Most participants described the need for a programme like “Ubuntu”, reporting that it would have been welcome when their children were younger particularly in the period just after diagnosis. The results will be published elsewhere.

“Baby Ubuntu”, an adapted version of “Ubuntu” for babies and young children with developmental disabilities, has been co-adapted using the ADAPT framework [25] to form the “Encompass” programme. The adaptation process and outcome will be published separately. This adaptation and implementation of “Baby Ubuntu” in a high-income context such as the UK is an example of a “decolonised healthcare innovation” as it brings a frugal innovation developed in a resource-constrained setting to a high-income setting such as the UK [26]. There is encouragement to test frugal innovations in the UK National Health Service (NHS) in particular, as it faces a workforce crisis and high constraints in resources [27]. Decolonisation in global health challenges dominant discourses about health created by those in power [28]. The adaptation of “Baby Ubuntu” does this by acknowledging the valuable innovations and knowledge created in low- and middle-income countries regarding optimal ways to holistically support parents of children with disabilities. It also challenges traditional “top-down” approaches common in high-income country healthcare systems by introducing a community-owned, participatory, cost-conscious and peer-led programme. This is part of a recent shift emphasising the importance of community participation in health interventions in high- and middle-income countries [29]. The next step is therefore to pilot the intervention in two settings in the UK NHS using a participatory approach [30], to assess the feasibility of delivering and evaluating the programme to inform a protocol for a larger-scale evaluation. The cost of running the programme will be explored too.

This protocol describes Encompass-2 — a non-randomised pilot and feasibility study.

### Objectives

#### Primary objective

To determine the feasibility and acceptability of delivering the co-adapted community-based group programme (“Encompass”) with parents/carers of children under 5 years with complex neurodisability in urban areas with high levels of social deprivation and ethnic diversity in England.To assess the feasibility of intervention delivery (i.e. recruitment, retention rates, acceptability as perceived by the parents/carers, facilitators and wider key NHS partners) to inform the next stage in the development of a large-scale evaluation of “Encompass”To assess intervention fidelity and participant adherence

#### Secondary objective

To determine the feasibility of carrying out an evaluation of the “Encompass” programme, which assesses health-related outcomes of parents/carers of children with complex neurodisability, as well as cost-effectiveness.To assess the proportion of participants who complete the post-intervention and follow-up assessmentsTo explore how participants experience the research visits and the acceptability of the study questionnaires/ assessmentsTo assess the appropriateness, acceptability and completeness of the outcome measuresTo assess the means and standard deviations of participants’ scores on the measures at baseline and post-intervention and to determine what pre-post effect sizes are obtained to inform sample size calculations for a future larger-scale evaluationTo record the cost of the “Encompass” programme delivery and pilot feasibility study phases

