### Sample size

The sample size of the study was generated based on a variety of literature and methods. Simple confidence interval calculations were used for the feasibility estimates research questions and qualitative justifications for the acceptability research questions.

As the objectives of the feasibility study relate to estimating a rate (i.e. the proportion of people) of those who completed follow-up questionnaires and attended the groups, it is suggested that confidence intervals may be calculated by relating the proposed sample size to the width of the confidence interval for the rate, using the following equation with *P* being the proportion one expects to see and *n* the intended sample size [58]:$$1.96 \times \surd (P \times (1-P)/n)$$

The standard error of a proportion depends on the value of the proportion itself, reaching its largest value when the proportion equals 0.50 [58]. The table below displays the width of confidence intervals across reference sample sizes for two values of proportion (Table 4):An estimation of the follow-up response rate questionnaires being 70%As estimation of group attendance (attending > 6 out of 10 modules) of 80%

**Table 4 Tab4:** Width of confidence intervals across reference sample sizes for two values of proportion (completion of follow-up questionnaires and group attendance)

*n*	Group configuration		*P*	CI_95_
12	Two groups of six each	Follow-up	0.70	0.26
		Attendance	0.80	0.23
16	Two groups of eight each	Follow-up	0.70	0.22
		Attendance	0.80	0.20
20	Two groups of 10 each or 3 groups of 6 or 7 each	Follow-up	0.70	0.20
		Attendance	0.80	0.18
24	Three groups of eight each	Follow-up	0.70	0.18
		Attendance	0.80	0.16
30	Three groups of 10 each	Follow-up	0.70	0.16
		Attendance	0.80	0.14

For a follow-up response rate of 70% in the feasibility study of 12 participants, we can be 95% confident that this estimate is accurate within + / − 26%. When the sample size is increased to 20 participants, the error in estimation is reduced to 20 percentage points. If increased to 24 participants, this is only slightly reduced to + / − 18%. An increase to 30 participants results in a marginal reduction to + / − 16%.

The above calculations relate to the feasibility rate estimates and suggest that a sample of 20 may be adequate.

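### Pre-post effect sizes from an uncontrolled sample of at most 20 are meant to inform the size of the larger evaluation, but they estimate the wrong quantity and are too imprecise for that use

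*Protocol article*

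**What the plan says.** The protocol article, under Objectives, Secondary objective, plans to obtain means and standard deviations of the measures at baseline and post-intervention and "to determine what pre-post effect sizes are obtained to inform sample size calculations for a future" larger-scale evaluation. The other items in that list concern completion, acceptability of the measures and cost. None gives another source for the target difference.

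The Background calls the study "a non-randomised pilot and feasibility study". The abstract states "We aim to recruit 20 parents/carers of children from two NHS trusts in England" and "Recruited parents/carers will attend the 10-modular, participatory group programme over a 6-month period". Everyone enrolled is offered the programme and no comparison group is described.

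The Sample size section derives 20 from the precision of two proportions, an expected 70% follow-up response and 80% attendance, and concludes: "The above calculations relate to the feasibility rate estimates and suggest that a sample of 20 may be adequate". It then gives a separate argument for the number of interviews. Neither argument addresses the precision of a change score. The Data analysis section summarises the scales by mean and SD.

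On context, the Intervention section says that families may join from the time of diagnosis. The Ethics section notes that parents at that stage may have mental health difficulties, denial and anxiety.

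**The concern.** There are two separate problems.

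The first is the quantity estimated. A controlled evaluation must detect a difference between groups. The change within one treated group equals the programme effect plus whatever change would have happened without it. The protocol's own account of the period after diagnosis makes such background change plausible for empowerment, wellbeing and quality of life over a six-month programme. The study cannot separate the two.

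The second is precision. Even with no background change, a standardised change from 20 or fewer pairs is too uncertain to size a trial on. Required sample size varies with the inverse square of the effect, so modest error in the effect becomes large error in the size.

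Preparing the larger evaluation is a main purpose of this study. If the observed effect becomes the target difference, the next trial could be well short of its intended power, or much larger than it needs to be.

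**Working it through.** **1. The plan's own figure.** Table 4 uses 1.96 × √(P(1−P)/n). At n = 20:
- follow-up, P = 0.70: 1.96 × √(0.21/20) = 0.2008 (stated 0.20)
- attendance, P = 0.80: 1.96 × √(0.16/20) = 0.1753 (stated 0.18)

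All ten entries of Table 4 reproduce. The justification is sound for what it covers, which is proportions.

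**2. Number of pairs.** At most 20. If the 70% planned for follow-up also applied post-intervention, 0.70 × 20 = 14. That carry-over is an assumption: Table 3 lists post-intervention and 3-month follow-up as separate time points, and no post-intervention rate is given. Both values are shown below.

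**3. Precision of an observed standardised change of 0.30** (an assumed value; change divided by the SD of change). With t = 0.30 × √n and n − 1 degrees of freedom, invert the noncentral t distribution and divide the limits by √n.

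| Pairs | t | Limits for noncentrality | 95% CI for effect |
|---|---|---|---|
| 20 | 1.342 | -0.680 to 3.330 | -0.15 to 0.74 |
| 14 | 1.122 | -0.904 to 3.108 | -0.24 to 0.83 |

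For an observed 0.50 the intervals are 0.03 to 0.96 (20 pairs) and -0.07 to 1.05 (14 pairs).

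**4. What this means for a trial size.** Assumptions, none stated in the protocol: two arms 1:1, individual allocation, two-sided alpha 0.05, 80% power, and pre-post correlation 0.5, so that change divided by its own SD is on the same scale as a between-group standardised difference. Size per arm = 2 × ((1.96 + 0.8416)/d)².
- d = 0.30: 174.4, so 175 per arm
- d = 0.74 (upper limit, 20 pairs; 0.7446 unrounded): 28.3, so 29 per arm
- d = 0.83 (upper limit, 14 pairs; 0.8307 unrounded): 22.7, so 23 per arm
- both lower limits are negative, so no finite size exists

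**5. How often the trial would be badly underpowered.** Let the true effect be 0.3 with no background change at all. Power falls below 50% when the size per arm is under 2 × (1.96/0.3)² = 85.4, that is, 85 or fewer. That size is chosen when the pilot estimate is at least 2.8016/√(85/2) = 0.43. From the noncentral t distribution, among pilots with a positive estimate:

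| Pairs | Estimate ≤ 0 | Under 50% power, given a positive estimate | Power 70–90%, given a positive estimate |
|---|---|---|---|
| 20 | 9% | 33% | 15% |
| 14 | 13% | 38% | 13% |

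Simulation of 200,000 pilots per case gives the same figures.

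**6. Sensitivity to the scale.** The standardised change equals d/√(2(1−r)). With true d = 0.3 and r = 0.7 it is 0.39. Using it as d gives 105 per arm instead of 175, with power 58%. With r = 0.3 it is 0.25, giving 245 per arm and 91% power. The error can go either way.

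**7. Sensitivity to background change.** The protocol gives no value, so this is a range only. If 0.1, 0.2 or 0.3 of an observed 0.5 would have occurred anyway, the 63 per arm planned on 0.5 has 61%, 39% or 20% power.

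**8. What the pilot SD can support.** The one-sided 80% upper limit is SD × √((n−1)/χ²), with χ² the 20th percentile on n − 1 degrees of freedom: 1.18 × SD at n = 20 and 1.23 × SD at n = 14.

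**The case against.** The strongest reply is that the protocol commits to little. Its verb is inform. A reader might infer that the pilot effect will by itself set the next sample size, but the text states no formula and no exclusive reliance. The same item collects means and SDs, which are proper pilot outputs. The target difference will finally be fixed in the later trial's own protocol. This stands as a limit on the point, but it does not remove it: the stated use of the effect sizes is sample size calculation, and nothing else is offered for the target difference.

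A reader might also infer that a chance near-zero result could end the programme. The documents do not support that. The traffic light criteria in Table 2 are recruitment, attendance, follow-up response and fidelity, and no outcome effect enters them.

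Regression to the mean is a tempting addition, but Table 1 sets no threshold on any outcome scale, so it should not be asserted. Background change after diagnosis is plausible from the protocol's own text, but its size is unknown.

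The larger evaluation's design is not fixed, so every per-arm figure is illustrative. The confidence intervals in step 3 do not depend on that design. Finally, intervals and other analysis detail may sit in a fuller protocol or analysis plan, so their absence from the article is not criticised here.

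**Conclusion.** The point holds at moderate severity. The protocol assigns to the pre-post effect sizes a use they cannot serve. They do not estimate a between-group difference, and with 14 to 20 pairs an observed 0.30 is compatible with anything from a small deterioration to a large improvement. The imprecision remains if all 20 respond. The 33% to 38% chance of under 50% power depends on the assumptions in steps 4 and 5 and is conditional on a positive estimate. The lack of a comparator matters to the extent that the larger evaluation is controlled; the protocol does look ahead to a trial (Theories and frameworks; Primary outcomes). The sample of 20, the primary outcomes and the progression criteria of this study are unaffected.

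**What to change.** Reword the secondary objective so that the pilot supplies, for planning the larger evaluation:
- the outcome SD, with an upper confidence limit (for example one-sided 80%, about 1.18 × SD with 20 participants and 1.23 × SD with 14)
- the pre-post correlation
- completeness and attrition

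State that pre-post change will be reported with its 95% confidence interval as description only, and will not be the basis for the target difference. Take the target difference from an important difference agreed beforehand with the PPI group and from published evidence.

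The cost is the wording of one objective and one added analysis sentence, with no new data. The downside is that the future trial may be planned larger. For a fixed difference in scale points, using the upper SD limit rather than the SD itself raises the size by a factor of 1.18² = 1.39 (20 participants) or 1.23² = 1.51 (14 participants).

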## Methods

This is a mixed-methods pilot and feasibility study that aims to determine the feasibility and acceptability of delivering and evaluating the “Encompass” programme to two groups of parents/carers of children with complex neurodisability (< 5 years) recruited from two NHS trusts in England serving urban areas with high levels of social deprivation and ethnic diversity. The protocol has followed reporting guidelines for pilot and feasibility trials from Thabane and Lancaster [31], who suggested utilising elements and adapting the SPIRIT (Standard Protocol Items: Recommendations for Interventional Trials) guidance [32] and the CONSORT extension to pilot trials [33]. Checklists for the SPIRIT and the CONSORT extension may be found in Additional files 1 and 2.

### Theories and frameworks

Four theoretical frameworks will guide the methodology of the study, namely: the Medical Research Council (MRC) framework for developing and evaluating complex interventions [34], the ADAPT guidance [25], the Theoretical Domains Framework [35] and the Context Compass Framework [36].

The pilot/feasibility study is embedded within the MRC framework for developing and evaluating complex interventions [34]. The “Encompass” intervention is a complex intervention due to the multiple components, expertise required to deliver it and its interactions with the wider systems. These systems include health, social and educational services, the local community and global perceptions around disability including stigma. This stage of the study will fall within the feasibility and develop intervention phases of the MRC framework while considering the core elements of context, developing and refining the programme theory, engaging interested parties and identifying key uncertainties. The programme theory has been developed in the form of a logic model using realist methodology and will be published elsewhere along with the process of adaptation.

Clearly defined prompts and questions in the ADAPT guidance aim to deepen the researcher’s understanding of adapting interventions for new contexts [25]. It is recommended to be used alongside intervention development guidance, in this case the MRC framework. The ADAPT guidance recommends evaluating feasibility through recruitment and retention rates, which have been included in the research questions.

Topic guides for qualitative data collection and the subsequent analysis will be guided by the Theoretical Domains Framework (TDF) for individual-level determinants that influence the implementation of the “Encompass” programme (e.g. participants and facilitators) [35]. When the study has a health equity lens, a greater emphasis on context has been recommended [37]. In order to appropriately determine both the setting and system contextual factors that influence implementation, the Context Compass framework will be utilised [36]. Topic guides may include questions about the fit or readiness of the setting to receive the “Encompass” programme, which will be particularly important to discuss with key NHS partners.

To pilot-test and assess the feasibility of the intervention, elements from the CONSORT extension to pilot and feasibility studies will be drawn upon [33], for example it is recommended that the primary aim of a pilot study relates to feasibility of proceeding to a definitive trial and that there be formal progression criteria to decide whether to proceed or not. The CONSORT extension will be used in combination with guidelines created by Lancaster and Thabane [38] which support the preparation and reporting of non-randomised pilot and feasibility studies by providing advice for adapting the CONSORT extension for non-randomised studies. The collection and analysis of qualitative data in this phase will be considered through the lens of O’Cathain et al.’s guidance on maximising the impact of qualitative research in feasibility studies for randomised controlled trials [39]. Feasibility studies aim to gain a deeper understanding of how the intervention works and to facilitate ongoing adaptation and preparation for larger-scale evaluations, and this is where qualitative data may be particularly valuable.

